**Methods:**

This study will be conducted in the Chronic Pain Rehabilitation Program (CPRP) at the James A. Haley Veterans Hospital, a unique inpatient program within the VA system. Participants will include up to 20 Veterans who receive a VR intervention as part of their physical therapy. A rating form containing qualitative and quantitative experiences will be administered following each VR session to assess feasibility and to provide descriptive information for the proposed hierarchy. Effect sizes will be calculated from intake and discharge measures for the primary outcome fear of movement and secondary pain and functional outcomes.

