### Participants and recruitment

All Veterans (*N* ≤ 20) enrolled in the CPRP over the 3-week data collection period will be recruited. Interested individuals will be consented in-person by the research staff. Given the pragmatic nature of this study, eligibility is consistent with the CPRP program. Inclusion criteria: (1) the presence of chronic pain syndrome (ICD-9-CM code 338.4) and experiencing psychosocial dysfunction and functional impairments due to chronic pain and (2) a negative urine drug screen for alcohol, illicit substances, and prescribed opioid or psychiatric medications. Exclusion criteria: (1) uncontrolled depressive symptoms; (2) actively suicidal; (3) uncontrolled psychotic symptoms; (4) a recent history of violent or aggressive behavior; (5) high fall risk; and (6) cardiac, pulmonary, or neurological contraindications [25, 26].

Each week, four Veterans graduate from the program and are discharged from the CPRP. Up to four new Veterans are then admitted into the CPRP. Enrollment includes up to 12 Veterans at a time. Demographic characteristics from a CPRP cohort study (*N* = 705) reported that Veterans were 50.08 ± 11.03 years old with an average pain chronicity of 13.02 ± 10.85 years, report baseline pain near the “severe” range (7/10) on a numeric rating scale 6.95 ± 1.65, primarily experience back pain (56.20%), are prominently male (79.80%), Caucasian (60.77%), on disability or retired (73.22%), slightly more likely to be married (51.63%), less likely to be prescribed opioids daily (39.46%), and experience “moderate” relief from opioid therapy [25]. The program attrition rate for non-compliance during this period was 14.89% (*N* = 105). Consistent with the VA mission to reduce high-dose opioid use, all Veterans must agree to begin an opioid taper upon CPRP admission when applicable.

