### Design

A type 1 hybrid design will be used to blend clinical effectiveness and implementation research to accelerate the proposed VR intervention into practice. Primary and secondary outcomes (Aim 2) will be assessed using a within-subjects pretest-posttest design. Qualitative pre-implementation data will be collected following each VR session. The VR intervention will be implemented as an adjunct part of graded exposure physical therapy (PT) sessions in the CPRP. For each session, participants will be assigned to use one of two VR head-mounted displays (HMD: Oculus Rift, Gear VR). VR assignment will be balanced secondary to equipment availability. Specifically, participants will participate in two sessions of Gear VR [27] for each session of Oculus Rift [28].

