### Analytic plan

All demographic characteristics, primary and secondary measures, will be described by the use of means and standard deviations for continuous variables and percentages for categorical variables. Multiple steps will be taken to handle missing data. Missing value patterns will be examined using Little’s Missing Completely at Random Test [61]. Missing data will be estimated using multiple imputations with demographic information and participant baseline scores on primary and secondary measures as predictors of missing items [62]. Up to 20% of missing data will be allowed for the proposed study based on evidence suggesting that standardized bias of mean changes is acceptable when using multiple imputation techniques in a small sample (*N* = 20) [63].

#### Aim 1

Describe the individual Veteran trajectories and APP intensity ratings across the proposed distraction-to-exposure hierarchy. Distributions of the Veteran-selected VR APPs (proposed movement intensity range of 1–6) will be calculated and plotted across all sessions over the course of the study. The frequency of individual Veteran trajectories will be counted to identify common patterns for the preferred level of movement. Veteran’s average self-reported intensity ratings for individual VR APPs will be plotted across sessions. Consistencies between the level of movement required to engage in the APP and self-reported intensity will be descriptively examined.

#### Aim 2

Estimate the within-subjects effect size and 95% CI for changes in fear of movement to provide insight into the likely magnitude of effect associated with the VR intervention. For the primary outcome (POQ-VA: fear of movement) the within-participant effect size calculations (*M*_post_ – *M*_pre_/SD_diff_) will be made along with 95% CIs to provide insight into the effect associated with VR utilization [64]. This step will also be completed for the FDAQ. Furthermore, the FDAQ mean difference from baseline and 95% CI will be calculated and compared to the established MCIC for this measure. The proportion of Veterans that experience clinically meaningful change will then be calculated. For secondary pain and functional measures, the effect sizes, mean differences from baseline with 95% CIs, and the proportion of participants that experience meaningful change will be examined. Data from secondary measures will be used to select optimal instruments for use with VR in a larger RCT.

#### Aim 3

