## Discussion

Studies have demonstrated the efficacy of using VR interventions as a means of pain distraction for people with acute [11, 16, 42] and to a lesser extent chronic pain [17]. Similarly, evidence suggests that graded exposure to feared movements via VR interventions can improve function among people with chronic pain [21, 22]. However, there is a lack of sufficient evidence from studies examining multiple VR APPS or varying simulation intensity levels, both of which have been identified as important directions for future VR research [16]. Moreover, no studies have examined distraction and exposure methods as part of a two-dimensional VR hierarchy. The proposed research addresses these gaps in the literature by utilizing multiple VR APPs requiring varying levels of movement that range from low-intensity pain distraction to a more active exposure to movement.

This study will inform the feasibility of a larger RCT examining the clinical utility of using VR to reduce fear of movement, pain, and increase function among Veterans with chronic pain. This will be accomplished in multiple ways. First, effect size estimates for improvement in fear of movement will be used to power a larger RCT. Second, effect size and clinically meaningful change on secondary outcomes will help in the selection of optimal scales for use with VR in the larger clinical trial [66]. Third, descriptive information collected on Veteran trajectories for the proposed hierarchy (i.e., APP selection, self-reported APP intensity) will assist in any necessary modifications so that Veterans are not over- or underexposed. Fourth, data collected using the daily rating form will provide useful information regarding Veterans with chronic pain using this technology. This will include whether 20 min is an appropriate length for VR exposure, experienced adverse events (e.g., cybersickness, falls), and facilitators (e.g., immersion, HMD preferences) or barriers (e.g., physical, psychological discomfort) to VR use [47, 66]. Additional qualitative information will help with the identification of any additional unforeseen factors.

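### The fear-of-movement effect size meant to inform the RCT's power is defined without a small-sample correction, so at N of 20 or fewer it exaggerates the effect by about 4 to 5% on average

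*Protocol article*

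**What the plan says.** The Abstract caps the sample: "Participants will include up to 20 Veterans who receive a VR intervention as part of their physical therapy". Under Design, the primary and secondary outcomes "will be assessed using a within-subjects pretest-posttest design".

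The Analytic plan, Aim 2, prints the estimator for the primary outcome (the POQ-VA fear scale) as post-treatment mean minus pre-treatment mean, over SD_diff. The outer brackets are missing in print, but the meaning is clear. These calculations "will be made along with 95% CIs to provide insight into the effect associated with VR utilization". The same step is planned for the FDAQ, and effect sizes are also planned for the secondary measures. The text states no small-sample correction and no method for the interval; it cites a source.

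The Discussion gives the use: "effect size estimates for improvement in fear of movement will be used to power a larger RCT".

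Two other statements bear on the effective sample size. Participants and recruitment reports historical programme attrition of 14.89% for non-compliance. The Analytic plan says "Up to 20% of missing data will be allowed for the proposed study", with multiple imputation.

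**The concern.** A mean change divided by its own estimated SD is not an unbiased estimate of the standardised effect. The sample SD is in the denominator, and in small samples this makes the ratio too large in magnitude on average. The bias is negligible in large samples but not entirely so at 20 or fewer.

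It matters because of the stated use. The sample size of a two-arm trial varies with one over the squared effect, so an exaggerated planning value makes the next trial smaller than it should be. The error has a known direction and size, and it is cheap to remove. The formula is printed in the article, so the point concerns a stated choice and not a detail left to another document.

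**Working it through.** The article gives no power, alpha, expected effect or SD, so there is no planned figure to reproduce.

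**Inputs from the article**
- n at most 20 (Abstract; Participants and recruitment).
- Attrition of 14.89%: 20 × (1 − 0.1489) ≈ 17.
- Missing-data allowance of 20%, read as loss of whole participants: 20 × 0.80 = 16.

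**Assumptions**
- Normally distributed change scores and complete data at each n.
- For the RCT illustration only: two-sided alpha 0.05 and 80% power. Neither is in the article.

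**Step 1: mean bias.** With m = n − 1, E[d] = δ / J(m), where J(m) = Γ(m/2) / [√(m/2) · Γ((m − 1)/2)]. The usual approximation is J ≈ 1 − 3/(4(n − 1) − 1).

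| n | Approximate J | Exact J | Mean inflation, 1/J − 1 |
|---|---|---|---|
| 20 | 1 − 3/75 = 0.960 | 0.960 | 4.2% |
| 17 | 1 − 3/63 = 0.952 | 0.952 | 5.0% |
| 16 | 1 − 3/59 = 0.949 | 0.949 | 5.4% |

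The bias is away from zero. On scales where improvement is a negative change (FDAQ, PCS, reverse-scored PSFS) the signed estimate is too low, and the magnitude is still overstated.

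**Step 2: bias beside sampling error.** At n = 20 and a true effect of 0.5, the mean estimate is 0.5/0.960 = 0.521, a bias of 0.02. The large-sample standard error is √(1/20 + 0.5²/40) = √0.05625 = 0.24, and the exact SD of the estimator is 0.25. The bias is therefore less than a tenth of the standard error. An observed 0.5 at n = 20 has a noncentral-t 95% interval of 0.03 to 0.96.

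**Step 3: effect on the RCT, if the value were used directly as a between-group effect.** At a true effect of 0.5, 63 per arm are needed. Planning on the mean estimate of 0.521 gives 58 per arm and 76.8% power instead of 80%. The mean is pulled up by the estimator's skewed distribution. From the noncentral t, the median estimate at n = 20 is 0.507, so the median implied shortfall is 1 − (0.5/0.507)² ≈ 2.7%. At n = 17 it is 3.2%. The chance that an n = 20 pilot overestimates the effect is 51%.

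**Step 4: interval coverage at n = 20, by method** (400,000 simulated samples per setting)

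| Construction | Coverage of a nominal 95% interval |
|---|---|
| d ± 1.96·√(1/n + d²/2n), true d 0 to 1.5 | 94.7 to 94.8% |
| Same form with the t critical value and d²/(2(n − 1)) | 96.2 to 96.5% |
| t limits for the mean change, divided by SD_diff | 95.0% at d = 0; 93.5% at 0.5; 91.3% at 0.8; 89.3% at 1.0 |
| Noncentral t | 95.0% |

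Of these, only the construction that ignores the uncertainty in SD_diff falls materially short, and only when the effect is not small.

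**The case against.** The strongest reply is that this is a descriptive pilot and that an uncorrected standardised change is a common statistic. The bias is a small fraction of the standard error, the plan already reports a 95% interval, and a single pilot is almost as likely to understate the effect as to overstate it. All of that is true, and it makes the point minor. It does not make the printed estimator unbiased, and the correction costs almost nothing.

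A second reply is that the correction misses the larger difficulty. The estimate is an uncontrolled pre-post change within a 19-day interdisciplinary programme, while the Discussion foresees an RCT against an active control. That stands. Removing a 4 to 5% bias does not make this the between-group effect on which such a trial is powered.

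A reader might also infer three stronger things that the article does not support:
- **That the 95% intervals will under-cover.** No interval method is stated, the cited source is not at hand, and an article may leave this to the analysis plan. The usual large-sample interval is close to nominal.
- **That the RCT will be 8 to 9% too small.** This comes from 1 − J² (7.9% at n = 20, 9.3% at n = 17), which puts the mean of a skewed estimator into a squared reciprocal. At a true effect of 0.5 the median shortfall is about 3%.
- **That the bias will reach 7.5%.** That is the value at n = 12. The cap of 20 permits so small a sample, but the cited attrition leads to about 17 and the missing-data allowance to 16.

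**Conclusion.** The point holds as a minor improvement. The stated estimator overstates the magnitude of the effect on average, by 4.2% at n = 20 and 5.0% at n = 17, and the Discussion names it as an input to the RCT's power. Under the assumed alpha and power, and a true effect of 0.5, planning on the mean uncorrected value would cost about 3 percentage points of power; the typical (median) loss is smaller. Sampling error is the greater uncertainty. An observed 0.8 at n = 20 has a 95% interval of 0.29 to 1.30 which, read as a between-group effect, spans 192 down to 10 per arm, against 25 at the point estimate.

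The figures rest on normal change scores and complete data. Multiple imputation would alter them somewhat. Nothing is concluded about how the intervals will be built.

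**What to change.** In the Analytic plan, Aim 2, report the Hedges-corrected effect for every outcome: multiply (M_post − M_pre)/SD_diff by 1 − 3/(4(n − 1) − 1). In the Discussion, say that the corrected value is the one carried into RCT planning, together with the confidence limit nearer zero. That wording matters because the numerically lower limit is the most optimistic one on the FDAQ, PCS and reverse-scored PSFS. The limit serves to show the range of plausible effects; when it is close to zero, as with an observed 0.5 at n = 20, it cannot size a trial by itself.

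A noncentral-t 95% interval is a suitable choice. It already refers to the true effect and should not be multiplied by the correction as well.

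**Cost.** Stated effects become about 4 to 5% smaller. The corrected estimate and its interval must be pooled across the imputed data sets, so the plan needs a sentence on that. The correction removes the mean bias, but the median then falls slightly below the truth (0.960 × 0.507 = 0.487 at a true 0.5 and n = 20), which is on the cautious side for planning. A further sentence should say that the result remains an uncontrolled pre-post effect and is not by itself the RCT's planning difference.

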## Discussion

Studies have demonstrated the efficacy of using VR interventions as a means of pain distraction for people with acute [11, 16, 42] and to a lesser extent chronic pain [17]. Similarly, evidence suggests that graded exposure to feared movements via VR interventions can improve function among people with chronic pain [21, 22]. However, there is a lack of sufficient evidence from studies examining multiple VR APPS or varying simulation intensity levels, both of which have been identified as important directions for future VR research [16]. Moreover, no studies have examined distraction and exposure methods as part of a two-dimensional VR hierarchy. The proposed research addresses these gaps in the literature by utilizing multiple VR APPs requiring varying levels of movement that range from low-intensity pain distraction to a more active exposure to movement.

This study will inform the feasibility of a larger RCT examining the clinical utility of using VR to reduce fear of movement, pain, and increase function among Veterans with chronic pain. This will be accomplished in multiple ways. First, effect size estimates for improvement in fear of movement will be used to power a larger RCT. Second, effect size and clinically meaningful change on secondary outcomes will help in the selection of optimal scales for use with VR in the larger clinical trial [66]. Third, descriptive information collected on Veteran trajectories for the proposed hierarchy (i.e., APP selection, self-reported APP intensity) will assist in any necessary modifications so that Veterans are not over- or underexposed. Fourth, data collected using the daily rating form will provide useful information regarding Veterans with chronic pain using this technology. This will include whether 20 min is an appropriate length for VR exposure, experienced adverse events (e.g., cybersickness, falls), and facilitators (e.g., immersion, HMD preferences) or barriers (e.g., physical, psychological discomfort) to VR use [47, 66]. Additional qualitative information will help with the identification of any additional unforeseen factors.

Examining the feasibility of this protocol will also be beneficial for Veterans, clinicians, and policymakers. Per the 2016 National Pain Strategy [67], the federal government’s first coordinated plan strives to reduce the burden of chronic pain in the USA. Variations in clinical practice and inadequate tailoring of pain therapies, as well as a reliance on relatively ineffective high-risk treatments, have contributed to the poor quality of care for people with pain [67]. If the aims of this research are achieved, VR will be used in combination with established pain management strategies to decrease pain and opioid use. VR has the advantage of being easily implemented both within VA healthcare settings as well as in Veterans’ own residences, where engagement in ongoing self-management approaches is often most challenging.

VR therapies are projected to have a $3.9 billion market size by 2023 [68], yet despite this tremendous public health burden, published research to date has not extended beyond pilot trials and case studies. Given the lack of large-scale RCTs examining the clinical effectiveness of VR, findings from the proposed study will present a key step to inform a larger RCT to validate our proposed hierarchy and compare it to an active control group (i.e., VR APPs with no known therapeutic value). This level of RCT evidence represents a necessary next step in the evolution of clinical VR research.

## Data Availability

Once completed, the final de-identified datasets from this study (qualitative and quantitative) and the VR user manual will be made available by the corresponding author upon reasonable request.

## Abbreviations

ADL: Activities of daily living
CBT: Cognitive behavioral therapy
CPRP: Chronic Pain Rehabilitation Program
FDAQ: Fear of Daily Activities Questionnaire
HMD: Head-mounted display
PCS: Pain Catastrophizing Scale
POQ-VA: Pain Outcomes Questionnaire-VA
PSFS: Patient-Specific Functional Scale
PT: Physical therapy
RCT: Randomized controlled trial
VA: Veterans Affairs
VR: Virtual reality
